**Level 2: Standardized CHM intervention**

The Level 2 intervention, employing a higher-intensity formula consisting of 5 to 11 herbs, is designed for participants experiencing moderate symptoms of depression, anxiety, and insomnia, defined by a PHQ-9 score ranging from 10 to 19, a GAD-7 score from 10 to 14, or an ISI score from 15 to 21. A Chinese medicine practitioner will prescribe the herbal formula based on the participant’s TCM syndrome. The Level 2 intervention includes three types of herbal formulas for excess syndrome, deficiency syndrome and deficiency-excess complex syndrome, respectively. The classification of these three syndromes will primarily rely on the clinical judgment of the Chinese medicine practitioner, who will consider the patients’ symptoms, signs, and other body constitutional characteristics. Importantly, all herbal formulas are standardized, which facilitates the evaluation of their effectiveness and allows for easy replication in future studies. Details of the three formulas are listed in
Table 2. The level 2 CHM intervention will last for 6 weeks, where participants will be instructed to take the herbal formula twice a day. Participants whose symptoms do not downgrade to mild level in their assessment score after level 2 intervention will be stepped up to receive the level 3 intervention, while other participants who downgrade to mild/minimal symptoms will be followed up for another 6 weeks to examine the short-term effects of the herbal formula intervention.

**Table 2. T2:** The composition of the herbal formulas (Level 2 intervention).

	Name	Ingredients	g/day
Excess syndrome	Jia Wei Xiao Yao San	Bupleuri Radix, Angelicae Sinensis Radix, Paeoniae Radix Alba, Atractylodis Macrocephalae Rhizoma, Poria, Glycyrrhizae Radix et Rhizoma, Moutan Cortex, Gardeniae Fructus	10
Deficiency syndrome	Gui Pi Tang	Ginseng Radix et Rhizoma, Jujubae Fructus, Ziziphi Spinosae Semen, Glycyrrhizae Radix et Rhizoma, Polygalae Radix, Zingiberis Rhizoma Recens, Angelicae Sinensis Radix, Atractylodis Macrocephalae Rhizoma, Poria cum Radix Pini, Astragali Radix, Longan Arillus	10
Deficiency-excess Complex syndrome	Huang Lian E Jiao Tang and Jiao Tai Wan	Coptidis Rhizoma, Scutellariae Radix, Paeoniae Radix Alba, Asini Corii Colla, Cinnamomi Cortex	10.3

**Level 3: Personalized CHM intervention combined with psychotherapy**

Level 3 intervention integrates an 8-week personalized CHM intervention and an 8-session psychotherapy. The CHM intervention will be modified based on the 3 herbal formulas employed in the Level 2 intervention, enhancing the personalization by adding up to 5 additional herbs to specifically address symptoms with the highest level of precision and intensity among the 3 levels of treatment. The psychotherapy will adopt an integrative body-mind-spirit (I-BMS) psycho-social approach, which emphasizes a holistic concept of health and recognizes the inter-connectedness between the body, mind and spirit. During the treatment, project social workers and counsellors will introduce I-BMS knowledge, mindfulness/body-mind physical exercises to enhance the mental health of the participants. The intervention aims to improve their mental well-being and self-management strategies through a combination of casework and groupwork approaches. The counselling treatment consists of eight sessions (1.5 hours each) which are expected to be completed within 12 weeks, followed by a 12-week post-intervention follow-up.

**2.5.3 Criteria for discontinuing or modifying allocated interventions**

All patients could voluntarily participate in and withdraw from the study at any time without any reason or consequences. The treatment will be discontinued if the patient encounter a serious adverse reaction.

**2.5.4 Strategies to improve adherence to interventions**

To improve adherence to the intervention, enrolled participants in Level 1 will be contacted bi-weekly, and those in Level 2 and 3 will be contacted weekly by phone as a reminder to take their medication. At the end of the intervention, participants will be required to return both the empty packets from consumed sachets and any sachets that remain unconsumed.

**2.5.5 Relevant concomitant care permitted or prohibited during the trial**

Participants will be advised to maintain their usual daily habits throughout the intervention, including their diet and physical activity levels.

### 2.6 Outcomes

**Primary outcomes**
a)
**Depression**
The Patient Health Questionnaire-9 (PHQ-9) instrument is a 9-item scale measuring different aspects and severity of depression. It asks participants how often they experienced depressive symptoms over the past 2 weeks. PHQ-9 comprises 5 categories: 0–4 indicates minimal depression, 5–9 mild depression, 10–14 moderate depression, 15–19 moderately severe depression, and ≥20 severe depression. In the present study, a PHQ-9 score of 10-19 (moderate and moderately severe depression in original classification) will be deemed moderate depression for easy administration. The Chinese version of PHQ-9 has been validated in Hong Kong adults with good reliability (Cronbach’s alpha: 0.82).
^
43
^
b)
**Anxiety**
The General Anxiety Disorder-7 (GAD-7) instrument is a 7-item scale modified from the diagnostic criteria of Diagnostic and Statistical Manual of Mental Disorders, fourth edition (DSM-IV) for screening generalized anxiety disorder and severity. The cut-off scores of GAD-7 are: 0–4 indicates minimal anxiety, 5–9 mild anxiety, 10–14 moderate anxiety, and ≥15 severe anxiety. The Chinese version of GAD-7 has been validated in general hospital outpatients with a Cronbach’s alpha of 0.90.
^
44
^
c)
**Insomnia**
The Insomnia Severity Index (ISI) includes seven items assessing: 1) sleep onset, 2) sleep maintenance difficulties, 3) satisfaction with the current sleep pattern, 4) interference with daily functioning, 5) noticeable impairment due to sleep problems, 6) degree of distress, and 7) concerns caused by sleep problems. A total score of 0–7 indicates “no clinically significant insomnia,” 8–14 suggests “subthreshold insomnia,” 15–21 is classified as moderate severity, and 22–28 indicates severe insomnia. The Chinese version of ISI has been shown a satisfactory content validity index of 0.94 and high internal consistency with a Cronbach’s alpha of 0.81.
^
45
^

**Secondary outcomes**
a)
**Health-related quality of life**
The 12-item short form survey (SF-12) measures health-related quality of life across 8 domains - physical functioning, role limitations due to physical health, body pain, general health perceptions, vitality, social functioning, role limitations due to emotional problems, and mental health. The Chinese version of SF-12 has been shown a good reliability with a Cronbach’s alpha of 0.828.
^
46
^
b)
**Perceived stress**
The Perceived Stress Scale (PSS-10) is a 10-item scale that measures an individual’s perception of stress over the past month. It assesses the degree to which situations are perceived as stressful, unpredictable, uncontrollable and overloading. Six negative items are scored from 0 (never) to 4 (very often), and 4 positive items are reversely scored. Total scores range from 0 to 40, with higher scores indicating greater perceived stress. The Chinese version of PSS-10 showed a stable two-factor structure with a satisfactory internal consistency (Cronbach’s alphas = 0.67 to 0.78).
^
47
^
c)
**Utilization of healthcare resources**
A questionnaire will record the participants’ help-seeking behaviors related to mental health and sleep issues over the past month, including: the types of healthcare professionals consulted, such as psychiatrists, psychologists, counselors, social workers, nurses, and general practitioners; the number of visits made to healthcare professionals; and the expenditures associated with help-seeking for mental health or sleep issues.d)
**TCM body constitution assessment**
A comprehensive TCM symptom questionnaire will be administered to evaluate changes in symptoms from the TCM perspective. The questionnaire will assess symptoms across four TCM examinations, such as psychiatric symptoms (e.g. anxiety, depression, irritability), somatic symptoms (e.g. headache, dizziness, fatigue), digestive-related symptoms (e.g. appetite, abdominal pain, constipation, diarrhea), and sleep-related symptoms. The questionnaire will also include tongue and facial inspection, and pulse assessment. Each symptom will be rated by a registered Chinese medicine practitioner based on how often the participant experienced the symptoms over the past 2 weeks on a 4-point scale from 0 (not at all) to 3 (nearly every day).e)
**Compliance rate**
The compliance rate, defined as the proportion of prescribed CHM sachets consumed by participants. Participants will be required to return both the empty packets of consumed sachets and any remaining unconsumed sachets after the end of intervention. Compliance rate will be calculated for each participant using the formula: (number of sachets consumed/total number of sachets prescribed) ×100%.f
)
**Adverse events (AEs)**
All participants will be instructed to report any unexpected symptoms or health issues that arise during the study. Adverse events (AEs) will be categorized by severity - mild, moderate, severe, and undesirable (including life-threatening, disabling, or fatal), and assessed for whether they are related to the intervention. A registered Chinese medicine practitioner will document any adverse events at each TCM body constitution assessment. Participants will be encouraged to contact the research team immediately if any undesirable adverse events occur between scheduled visits. Standard operating procedures will be implemented to manage adverse events:1)Mild AEs potentially related to the intervention: The drug dosage may be reduced by half, with a follow-up assessment scheduled three days later by a registered Chinese medicine practitioner. If symptoms improve, participants may continue with the reduced dosage, with a possible return to the full dosage based on clinical judgment. If symptoms persist or worsen, the medication will be discontinued.2)Moderate AEs potentially linked to the intervention: The medication will be immediately stopped, and a follow-up assessment will occur after three days. If symptoms improve, a reduced dosage may be recommended, with consideration for returning to the full dosage based on clinical judgment. If symptoms do not improve or worsen, the medication will be discontinued.3)Severe AEs require immediate discontinuation of the drug. Reintroduction at full dosage will only be considered if the events are determined to be unlikely related to the intervention and once symptoms have fully resolved.All details of each adverse event will be recorded, including the nature (intervention-related or not), severity, duration, frequency, and any subsequent actions taken.

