**Level 1: Herbal Tisane**

The Level 1 intervention, utilizing a low-intensity tisane including four herbs, is designed for participants with mild symptoms of depression, anxiety, and insomnia, defined by a PHQ-9 score ranging from 5 to 9, a GAD-7 score from 5 to 9, or an ISI score from 8 to 14. A Chinese medicine practitioner will prescribe the herbal tisane based on the participant’s main complaints. The Level 1 program includes three types of herbal tisanes for depression, anxiety, and insomnia respectively. Details of these tisanes are listed in
Table 1. The level 1 intervention will last for 6 weeks, where participants will be instructed to take the tisane twice daily. Upon completion of the six-week intervention, participants whose main complaints escalate to moderate level will be stepped up to receive the level 2 intervention, while other participants who present with mild/minimal symptoms will be followed up for another 6 weeks to examine the short-term effects of herbal tisane intervention.

**Table 1. T1:** The composition of the herbal tisane (Level 1 intervention).

	Latin Pharmaceutical Name	Chinese name	g/sachet
Depression Tisane	Curcumae Radix	Yujin	2
	Paeoniae Radix Alba	Baishao	3
	Fructus Tritici Levis	Fuxiaomai	4
	Acanthopanacis Senticosi Radix et Rhizoma Sue Caulis	Ciwujia	3
Anxiety Tisane	Nelumbinis Plumula	Lianzixin	0.3
	Paeoniae Radix Alba	Baishao	2
	Margaritifera Concha	Zhenzhumu	5
	Fructus Tritici Levis	Fuxiaomai	4
Insomnia Tisane	Coptidis Rhizoma	Huanglian	0.6
	Cinnamomi Cortex	Rougui	0.3
	Margaritifera Concha	Zhenzhumu	5
	Poria cum Radix Pini	Fushen	3

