**Secondary outcomes**									
SF-12	✓	✓	✓	✓	✓	✓	✓	✓	✓
PSS-10	✓	✓	✓	✓	✓	✓	✓	✓	✓
Utilization of healthcare resource	✓	✓	✓	✓	✓	✓	✓	✓	✓
TCM assessment	✓	✓	✓	✓	✓	✓	✓	✓	✓
Compliance rate				✓	✓	✓			
Adverse events				✓	✓	✓			

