**Exploratory outcomes**									
Sample collection		✓			✓				
IBS-SSS		✓			✓				
Wearable device		✓			✓				
BMSWBI			✓			✓			✓

Note: A1_bs: Baseline assessment at level 1 intervention; A1_imd: Assessment immediately after level 1 intervention; A1_6w: Assessment 6 weeks after level 1 intervention; A2_bs: Baseline assessment at level 2 intervention; A2_imd: Assessment immediately after level 2 intervention; A2_6w: Assessment 6 weeks after level 2 intervention; A3_bs: Baseline assessment at level 3 intervention; A3_imd: Assessment immediately after level 3 intervention; A3_12w: Assessment 12 weeks after level 3 intervention. PHQ-9, Patient Health Questionnaire-9; GAD-7, General Anxiety Disorder-7; ISI, Insomnia Severity Index; SF-12, 12-Item Short Form Survey Instrument; PSS-10, Perceived Stress Scale-10; TCM, Traditional Chinese Medicine; IBS-SSS, irritable bowel syndrome-symptom severity score; BMSWBI, Body-mind-sprit Well-being Inventory.

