### 2.12 Blinding

Blinding of participants is not feasible for this trial due to the nature of the interventions. The research personnel responsible for delivering the CHM intervention cannot be blinded either. To mitigate potential bias, the clinician-rated TCM body constitution assessment and all objective outcomes, including data from wearable devices and the collection of biological samples, will be conducted by research personnel who are blinded to both the study design and participant group allocation. These assessors will have no role in delivering the intervention, and all participants will be instructed to conceal their allocation status during these assessments.

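### The printed schedule has no adverse-event check inside any treatment level, although the adverse-event procedures can act only during treatment

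*Protocol article*

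**What the plan says.** **Procedures (Protocol article, section 2.6, Adverse events).** Mild AEs possibly due to the intervention may lead to a reduced dose, with reassessment three days later. For moderate AEs: "The medication will be immediately stopped, and a follow-up assessment will occur after three days". Severe AEs require discontinuation. AEs are a secondary outcome, and each is to be judged for its relation to the intervention.

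**Who records AEs, and when.** The same section states: "A registered Chinese medicine practitioner will document any adverse events at each TCM body constitution assessment". It also tells all participants to report unexpected symptoms or health issues, without saying how soon. The only prompt for speed is: "Participants will be encouraged to contact the research team immediately if any undesirable adverse events occur between scheduled visits". In that section, *undesirable* is the category above severe and includes life-threatening, disabling and fatal events.

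**Schedule (section 2.7, Table 3).** The TCM assessment is ticked at all nine timepoints: baseline, end of level and follow-up for each of the three levels. The row "Adverse events" is ticked at the three end-of-level points only. The table note defines these by example as "A1_imd: Assessment immediately after level 1 intervention".

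**Contacts during treatment.** Section 2.13 mentions TCM tele-consultations at stages within the intervention period and points to Table 3 and Figure 3 for the detail. Section 2.5.4 plans bi-weekly calls at Level 1, and says that "those in Level 2 and 3 will be contacted weekly by phone as a reminder to take their medication". Section 2.13 gives retention and complete follow-up as a second purpose of these calls.

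**Blinding (section 2.12).** TCM assessments are made by personnel blinded to design and allocation, and "all participants will be instructed to conceal their allocation status during these assessments".

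**The concern.** A dose can be reduced or stopped only while doses remain. The section 2.6 procedures therefore presuppose that staff learn of an AE during the level in which it arises. The one place where staff are told to document AEs is the TCM assessment, and the schedule puts none between the start and the end of a level. At the end-of-level visit, nothing at that level is left to reduce or stop.

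Two things are at stake. First, procedures meant to protect participants may go unused for events that resolve, or are tolerated, before the end of the level. Second, AE frequency would rest on volunteered reports plus recall over six weeks or more. That kind of ascertainment tends to miss mild and moderate events. The introduction and discussion both present fewer side effects as an attraction of this type of treatment, so a low AE count would be read as supporting evidence.

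**Working it through.** The plan states no figure to reproduce. The check is a count of scheduled contacts against treatment length.

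**1. Treatment lengths (section 2.5.2).**
- Level 1: "The level 1 intervention will last for 6 weeks", so 6 × 7 = 42 days.
- Level 2: 6 weeks, so 6 × 7 = 42 days.
- Level 3: 8 weeks of herbs, so 8 × 7 = 56 days. Counselling is expected to finish within 12 weeks (12 × 7 = 84 days).

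**2. Scheduled AE checks strictly inside a level.**

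| Reading | Level 1 | Level 2 | Level 3 |
|---|---|---|---|
| Narrow: AE row of Table 3 | 0 | 0 | 0 |
| Broad: every TCM assessment in Table 3 | 0 | 0 | 0 |

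The broad reading adds baseline and follow-up visits, but none during treatment. The note to Figure 3 lists the same nine timepoints.

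**3. Time from first dose at a level to the scheduled AE record.** About 42 days at Levels 1 and 2. At Level 3 it is 56 days, or up to 84 if the end-of-level visit waits for counselling to finish.

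**4. Phone calls strictly inside a level.** Calls that coincide with the end of treatment are not counted.
- Level 1, reading bi-weekly as every two weeks: weeks 2 and 4, so 2. Twice-weekly calls would give more.
- Level 2, weekly: weeks 1 to 5, so 5.
- Level 3, weekly over the herb course: weeks 1 to 7, so 7.

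Neither section that describes these calls gives AE enquiry as a purpose. Level 3 also has eight counselling sessions, likewise without a stated AE role.

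**5. Statements that do not fit together.**
- Section 2.6 ties AE documentation to every TCM assessment (nine timepoints in Table 3). The AE row has three.
- Section 2.13 describes TCM tele-consultations during the intervention period. Table 3, to which it refers, has none inside a level.
- The numbered procedures in section 2.6 cover mild, moderate and severe AEs. The prompt for immediate contact names a different category.
- Section 2.12 asks participants to conceal allocation at the TCM assessment. Section 2.6 has AEs documented there, and each AE must be judged for relatedness, which is hard without knowing whether the participant is taking herbs.

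**The case against.** The strongest reply is that this is a journal article. It gives the purpose of the calls, not their full content. It refers to standard operating procedures for AEs, and call scripts normally sit in a fuller document. Section 2.13 can also be read as promising on-treatment TCM assessments, at which section 2.6 would have AEs documented. The drawing in Figure 3 was not available for this review; only its note was.

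Much of this stands, and it limits what may be inferred.
- A reader might conclude that nobody asks about AEs until treatment ends. The document does not say so: the content of the calls is unstated, not shown to exclude AEs.
- A reader might conclude that only the lower grades depend on volunteered reports. Between visits every grade does, and the general reporting instruction covers health issues broadly. The grades differ only in the encouragement to make contact at once.
- A reader might say that there is no AE record between first and last dose. That holds within a level. Participants who step up have a record at the end of the earlier level, before further herbs.
- A reader might take three days as a deadline for detecting an AE. It is the interval from the dose change or stop to reassessment.
- Under-reporting is a risk of this form of ascertainment. Nothing in the document demonstrates it.

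The reply does not remove the core point. The article prints a complete assessment table, a detailed AE procedure, and the frequency and purposes of the calls. The difficulty lies in how these stated parts fit together, not in an omitted detail.

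**Conclusion.** The point holds in a limited form. As printed, the schedule contains no AE check within any level: 0 in 42, 42 and 56 days of herbs. That sits badly with procedures that can act only on treatment, and it conflicts with what sections 2.6 and 2.13 say about when TCM assessments occur and what is recorded at them. If Table 3 is followed as written, on-treatment AEs are known only through participants' own reports and end-of-level recall. This risks under-ascertaining mild and moderate events and leaving the section 2.6 procedures unused.

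The conclusion rests on Table 3 being the operative schedule and on the Figure 3 drawing adding no timepoint beyond those in its note. The call counts of about 2, 5 and 7 assume that bi-weekly means every two weeks. The size of any under-count cannot be estimated from the document.

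**What to change.** 1. Reconcile sections 2.6 and 2.13 with Table 3. State whether any TCM assessment takes place inside a level, and at which assessments AEs are recorded.
2. Add one standard open AE question to the phone calls already planned in sections 2.5.4 and 2.13. Record onset date and grade, and show these contacts in the AE row of Table 3. If the calls already include such a question, say so.
3. Reconcile the prompt for immediate contact with the grades that have on-treatment procedures. Which clinical rule should apply is for the investigators to decide; the passages need to agree.
4. Reconcile the concealment instruction in section 2.12 with section 2.6, stating who documents AEs and who judges relatedness.
5. Section 2.1 reports recruitment complete and data collection expected to end in July 2025, so much of the treatment may already have been given. For that treatment, report AEs as volunteered or as recalled at the end of each level, and describe the ascertainment method beside the rates.

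The cost is a short call script, a data-capture form and an amendment, since the calls are already planned. The calls become slightly longer and reported AE counts will probably rise. AEs collected before and after the change should not be pooled without comment.

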**Exploratory Outcomes**
a)
**Blood sample**
The blood sample will be analyzed for hormone levels, inflammatory markers, neurotransmitter levels, and other relevant indicators. The blood test will also include complete blood count and parameters for liver and renal function. Assessment of blood biomarkers will help evaluate the physiological impacts of the intervention objectively.b)
**Urine sample**
The urine sample will be analyzed for metabolites, markers of oxidative stress, and other relevant indicators. This will involve assessing metabolomic profiles, identifying metabolites related to mental wellness, measuring reactive oxygen species levels, evaluating antioxidant capacity, and examining renal function markers and inflammatory markers.c)
